### Phase 1: interim assessments

During week 6, one training session will be replaced by interim assessments. Participants will perform a CPET and, after at least 1 h of rest, a Borg cycle strength test (BCST) [15, 48]. These assessments will provide updated MAP and maximum mean power output for 6 s (MPO_6_) data to optimize exercise intensities for MICT and HIIT in the following mesocycle. If a participant is already exercising at or above the intensity estimated from the interim assessment, the higher training intensity load will be kept. We refer to the outcomes section for further information of these assessments.

### Phase 1: supervision

All exercise sessions will be held and supervised by an experienced health care professional, such as physiotherapists, exercise physiologists, or other health care professional with equivalent expertise. All intervention providers will receive training on exercise intervention protocols to ensure standardization among centres. Instructors will give preparatory information during the training sessions, e.g., “In five seconds, increase your pedalling cadence up to 85 RPM”. Encouragement will be given during the sessions but be kept modest to not push the participants to exceed the intensity.

### Intervention arm: supramaximal HIIT

Following the warm-up, participants will perform 10 min of supramaximal HIIT. Supramaximal HIIT is performed as 10 × 6 s intervals against an individualized TPO. Since it takes approximately 6 s for the bike to apply the necessary breaking resistance to reach the TPO, each interval is programmed to last 12 s with a 48-s recovery between intervals. The first 20 s of the recovery is passive, while the latter 28 s are active at 30% of MAP. Target pedalling cadence for the intervals is 80–90 RPM and 50–70 RPM for the active recovery. Thus, regardless of individual capability, pedalling cadence will be even and controlled throughout the training sessions. If a participant is not capable of pedalling at 80–90 RPM, a lower cadence of 60–70 RPM will be allowed. Would a participant not be able to complete a 12-s interval, they will be instructed to not pedal during the next interval but only during the 48-s recovery phase. Then, the participant can continue with the following intervals or every-other interval, as based on instructor and participant judgement.

Including the warm-up and cool-down, the session duration is 20 min. Initial TPO for the supramaximal HIIT intervals is set at 60% of the MPO_6_ derived from a BCST (see “ Outcomes” section). The intensity and number of intervals (total training session duration) will be increased according to an escalation procedure (Table 1). The initial TPO of 60% of MPO_6_ is considered a familiarization session, and the intention is to increase the intensity to 80% of MPO_6_ in session 3 if the general progression criteria outlined in Table 1 are fulfilled.

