## Methods: interventions

### Phase 1

Eligible participants will be randomized to perform either supramaximal HIIT (intervention arm) or MICT (active control arm) on a stationary bicycle (Smart ZBike, Zycle, Valencia, Spain) coupled to a tablet. For both arms, training is performed two to three times per week for a total of 30 sessions (Table 1) using a group format with groups of four to eight participants at the same time. Group training will be conducted in designated rooms at a training facility. Visual supporting information (additional file 4, Figure S4-S5) will be displayed on the tablet and will include the session elapsed time, elapsed time per programmed phase, revolutions per minute (RPM), and target power output (TPO).

**Table 1 Tab1:** Overview of exercise progression and progression criteria for supramaximal HIIT and MICT during phase 1

Block	Week	Session	HIIT % of MPO_6_	MICT % of MAP	General progression criteria		
	**0**	**Baseline testing**			**Criteria TPO escalation**	**HIIT**	**MICT**
**Mesocycle 1**: focus on intensity and duration (only MICT)	**1**	1	60%	50%	Able to maintain minimum RPM last interval/minute	80	60
		2	70%	55%	Exertion (RPE 6–20)	≤ 17	≤ 13
	**2**	3	80%	60%	Dyspnea (0–10)	≤ 7*	≤ 5
		4	#	¤	Note: Exertion and dyspnoea are assessed at the end of the last interval/minute		
	**3**	5	#	+ 2 min			
		6	#	¤			
	**4**	7	#	+ 2 min	**TPO progression criteria**		
		8	#	¤	**# Supramaximal HIIT % of workload**		
	**5**	9	#	+ 2 min	RPE ≤ 14 and dyspnoea ≤ 3	+ 5 to 10%	
		10	#	¤	RPE 15–17 and dyspnoea 4–7	+ 2.5 to 5%	
	**6**	11	#	+ 2 min	If RPE 18 or dyspnoea 8	Keep same	
		12	**CPET and BCST**		If RPE 19 or dyspnoea 9	-2.5 to -5%	
**Mesocycle 2**: increased frequency. Focus on increasing duration and intensity	**7**	13	#	¤	If RPE 20 or dyspnoea 10	-5 to -10%	
		14	#	¤	**¤ MICT % of workload**		
		15	#	¤	RPE ≤ 11 and dyspnoea ≤ 3	+ 5 to 10%	
	**8**	16	+ 1 interval	+ 2 min	RPE 12–13 and dyspnoea 4–5	+ 2.5 to 5%	
		17	#	¤	If RPE 14 or dyspnoea 6	Keep same	
		18	#	¤	RPE ≥ 15 or dyspnoea 7	-2.5 to -5%	
	**9**	19	+ 1 interval	+ 2 min	RPE ≥ 16 or dyspnoea ≥ 8	-5 to -10%	
		20	#	¤	Note: The highest rating informs the progression decision		
		21	#	¤			
	**10**	22	+ 1 interval	+ 2 min	**Duration progression criteria**		
		23	#	¤			
		24	#	¤	**Supramaximal HIIT duration**		
	**11**	25	+ 1 interval	+ 2 min	RPE ≤ 17 and dyspnoea ≤ 7	+ 1 interval	
		26	#	¤	If RPE 18 or dyspnoea 8	Keep same	
		27	#	¤	If RPE ≥ 19 or dyspnoea ≥ 9	- 1 interval	

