	**12**	28	+ 1 interval	+ 2 min	**MICT duration**		
					RPE ≤ 13 and dyspnoea ≤ 5	+ 2 min	
		29	#	¤	If RPE 14 or dyspnoea 6	Keep same	
		30	#	¤	RPE ≥ 15 or dyspnoea ≥ 7	- 2 min	
	**13–14**	**Follow-up testing**			Note: The highest rating informs the progression decision. Duration is only increased if TPO is ≥ 80% MPO_6_ for HIIT, or 60% of MAP for MICT		

An overview of the intensity, duration, and their progression criteria to be used in phase 1. # indicates progression of supramaximal HIIT intensity based on criteria outlined in the table. ¤ indicates progression of MICT intensity based on criteria outlined in the table. HIIT intensities are expressed in % of MPO_6_ derived from the BCST while MICT intensities are expressed in % of MAP derived from a CPET. *BCST* Borg cycle strength test, *CPET* Cardiopulmonary exercise test, *HIIT* supramaximal high-intensity interval training, *MAP* maximal aerobic power, *MICT* moderate intensity continuous training, *MPO*_*6*_ maximal mean power output for six seconds, *RPE* rating of perceived exertion, *RPM* revolutions per minute, *TPO* target power output

^*^Based on our acute supramaximal HIIT preliminary data [17] and due to the short duration of the interval, a higher dyspnoea score cut-off is used compared to ERS guidelines [9]

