#### Anaerobic exercise capacity

Anaerobic exercise capacity will be assessed as intensity (absolute workload (watts), relative (% of MAP)) at the final stage during a BCST and as estimated MPO_6_. End-exercise and iso-time parameters, e.g., VO_2_ (ml/min/kg), ventilation (L/min), dyspnoea and RPE, will also be assessed, and presented as absolute value and as percentage of peak value obtained during CPET.

The BCST [48] is a submaximal cycle ergometer test that is used to estimate maximum mean power output for 30 s (MPO_30_) without an all-out effort. The BCST consists of 30-s efforts with increasing intensity, interspersed with 30-s passive recovery between each effort. With a target pedalling cadence of 80–90 RPM, participants cycle until they score an RPE of ≥ 17, or when they cannot keep the target cadence (< 75 RPM for 5 s). Would a participant continue until they cannot keep the target cadence or stop due to exhaustion at baseline testing, a RPE of 17 will not be used as a stopping criterion in follow-up testing. If a participant cannot maintain a cadence of 80–90 RPM during a familiarization bout, a lower (60–70) RPM will be used. In this case, the target cadence stopping criteria will be < 55 RPM for 5 s. Standardized encouragement will be given during the test.

We have tailored the test to our population of interest by modifying the initial load (15–50 W) and rate of increase (15–50 W) compared to the original BCST performed in young healthy adults [48]. The initial load and rate of increase is set depending on the participant’s previously determined MAP, where the aim is to reach a RPE of 17 after four to six stages. Incomplete 30-s stages with ≥ 10-s duration will be considered for the MPO_6_ calculation, by adding a certain load corresponding to the percentage of the completed stage (i.e., 15 s completed at 50 W increase will add 25 W to the last completed stage). The MPO_6_ is estimated by multiplying the power during the last completed stage by 1.75 as previously described [15] and successfully used in our research group in people with COPD [17, 78, 79].

The BCST has been shown to be feasible and effective in older adults to estimate the MPO_6_ and has in our research group also been used successfully in people with COPD as a test and to prescribe supramaximal HIIT. In our feasibility trial, the intensity during the last BCST stage was, on average, 150% of MAP (*n* = 32) [78, 79]. Subsequently, the MPO_6_ was on average 260% of MAP.

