#### Feasibility of interventions

Feasibility of the training programs will be assessed and evaluated between groups using both quantitative and qualitative measurement methods:Completion rate is determined by the total number of participants still performing the exercise training intervention at 12-week and 24-month follow-up. Reasons for non-completion, i.e., dropouts, are also obtained.Attendance rate is determined by the total number of attended sessions divided by total number of sessions prescribed, presented as a percentage. Reasons for non-attendance are also obtained.Adherence to exercise duration is determined as the adherence to the predefined intervals/minutes of the exercise training. Reasons for non-adherence are also obtained.Adherence to exercise intensity is determined as the adherence to the prescribed intensity of the exercise training. Reasons for non-adherence are also obtained. Exercise intensity (absolute workload (W), relative intensity (% of MAP, % of MPO_6_), the level of dyspnoea and leg fatigue (0–10, arbitrary units) on the [47] CR10 scale [47], and perceived exertion (6–20, arbitrary units) on the [47] RPE scale [60]) measured throughout the intervention will be reported. In addition, approximately 5 min after each exercise session, a session RPE [113] will also be collected using the [47] CR10 scale.Attendance rate for resistance training is determined as the self-reported total number of attended sessions divided by total number of sessions prescribed, presented as a percentage.Adherence to resistance training is determined as the self-reported adherence to the predefined number of exercises and number of sets.Exercise fidelity is determined as the incidence of exercise sessions requiring modifications, defined as any deviation from the prescribed exercise such as change in duration, intensity, or cadence.Occurrence and assessment of the severity of adverse events will be documented. Severity of adverse events will be rated into four different categories: (1) minor and temporary, (2) serious symptoms (potential risk of severe injury or life-threatening, (3) manifest injury or disease, and (4) death, as previously described [114]. An adverse event rate will be calculated for each participant as the total number of sessions during which any adverse events occurred divided by the total number of attended sessions.Participant satisfaction with the performed exercise training (supramaximal HIIT / MICT) will be recorded by adaptation of an existing patient satisfaction questionnaire previously used for cycling exercises in COPD [115] (see Tables S3 and S4, additional file 4).

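### Table 1 sets one HIIT cadence minimum of 80 RPM for raising target power, which participants on the permitted 60–70 RPM cannot meet without an instructor override

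*Protocol article*

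**What the plan says.** All references are to the protocol article.

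- **Cadence in HIIT** (Intervention arm: supramaximal HIIT). "Target pedalling cadence for the intervals is 80–90 RPM and 50–70 RPM for the active recovery". The same section then makes an allowance: "If a participant is not capable of pedalling at 80–90 RPM, a lower cadence of 60–70 RPM will be allowed".
- **Power progression** (Methods: interventions, Table 1, general progression criteria). The first criterion for raising target power output (TPO) is "Able to maintain minimum RPM last interval/minute", with 80 printed for HIIT and 60 for MICT. No second HIIT value is given.
- **The step to working load** (Intervention arm: supramaximal HIIT). Training starts at 60% of MPO6. The rise to 80% is planned "in session 3 if the general progression criteria outlined in Table 1 are fulfilled".
- **Added intervals** (Table 1, note to the duration criteria). "Duration is only increased if TPO is" at least 80% of MPO6 for HIIT or 60% of MAP for MICT.
- **Override** (Methods: interventions, Phase 1). The criteria are to be followed as far as possible. Instructors may depart from them where they judge it necessary, must record and justify each departure, and are told to use the option sparingly. The examples are people who habitually rate high or low, and day-to-day variation in well-being.
- **The same people in the exercise test** (Anaerobic exercise capacity). "If a participant cannot maintain a cadence of 80–90 RPM during a familiarization bout, a lower (60–70) RPM will be used", and the cadence limit for stopping the test is lowered for them, to below 55 RPM for 5 s.
- **Fidelity** (Feasibility of interventions). A session requiring modification is "defined as any deviation from the prescribed exercise such as change in duration, intensity, or cadence".

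**The concern.** The protocol creates a subgroup within the HIIT arm, those who train at 60–70 RPM, and then sets a progression criterion that this subgroup cannot meet while training as permitted. Intensity is the contrast the trial is built on, and Table 1 is the rule by which it is delivered. If the rule is applied as printed, these participants miss the intended working load and, through the duration note, the added intervals, even when their exertion and dyspnoea ratings are low. If it is not applied, progression rests on an override written for other situations. The same type of participant could then receive a different dose from different instructors or at the two centres.

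The conflict lies in one arm only. The MICT minimum of 60 RPM falls inside the MICT target range of 60–70 RPM.

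**Working it through.** The protocol states no figure for this point, so there is none to reproduce. The check is a comparison of rules, followed by the dose that each reading implies.

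**1. Do the ranges overlap?** Permitted lower HIIT cadence: 60–70 RPM. Table 1 minimum for HIIT: 80 RPM. Gap: 80 − 70 = 10 RPM. They do not overlap. For MICT, the minimum of 60 equals the lower end of the 60–70 target, so there is no conflict.

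**2. What the criterion controls, read literally.** Failing it blocks the step to 80% of MPO6, because that step is conditional on the general criteria. Staying below 80% of MPO6 then fails the duration note, so no intervals are added.

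**3. Intensity relative to MAP.** The Anaerobic exercise capacity section gives MPO6 as 260% of MAP on average in the feasibility trial. This agrees with its own inputs: 150% × 1.75 = 262.5%.
- 60% of MPO6: 0.60 × 260 = 156% of MAP.
- 80% of MPO6: 0.80 × 260 = 208% of MAP.
- Shortfall: (208 − 156) / 208 = 25%. The load is still above MAP.

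**4. Phase 1 interval work per affected participant, worst case.** One unit is one interval at 100% of MPO6. Session 12 is replaced by testing, leaving 29 training sessions. Table 1 adds one interval at sessions 16, 19, 22, 25 and 28.
- Intervals with tabled progression: 14 × 10 + 3 × (11 + 12 + 13 + 14 + 15) = 140 + 195 = 335.
- Work with tabled progression: session 1 at 60%, session 2 at 70%, the remaining 315 intervals at 80%: 10 × 0.6 + 10 × 0.7 + 315 × 0.8 = 6 + 7 + 252 = 265 units.
- Work if held at the start: 29 × 10 = 290 intervals at 60%: 290 × 0.6 = 174 units.
- Ratio: 174 / 265 = 0.66, about 34% less.

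MPO6 cancels in this ratio, so the 34% does not depend on the 260% figure. It does assume no override, no rise at the sessions marked #, no effect of the week-6 retest, and a comparator who gains every tabled interval and stays at 80%.

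**5. Effect on the arm.** The share *p* of HIIT participants on low cadence is not given. I assume 2% to 30%, all held at 60% with no override. Mean session-3 target = 80 − 20*p* (% of MPO6); relative fall = 20*p* / 80.

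| Assumed share | Mean target (% of MPO6) | Relative fall |
|---|---|---|
| 2% | 79.6 | 0.5% |
| 5% | 79.0 | 1.25% |
| 10% | 78.0 | 2.5% |
| 20% | 76.0 | 5% |
| 30% | 74.0 | 7.5% |

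This covers the session-3 target only, not later power steps or added intervals.

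**The case against.** A reader might infer that these participants can never progress, that the rule fixes them at the familiarisation load, and that the HIIT arm is therefore under-dosed and its contrast with MICT diluted. The documents do not support that reading, for several reasons.

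- **The criteria can be overridden.** Instructors may depart from them, and the examples are introduced as examples, so cadence is not excluded. This stands against any claim of a permanent block. It does not remove the conflict: a recorded exception, to be used sparingly, would be needed repeatedly for a subgroup that the protocol itself anticipates.
- **The later power steps may not depend on cadence.** The rows defining the # steps list only exertion and dyspnoea, and the general criteria are tied expressly to the session-3 step. On that reading a participant at 60% can still climb. With steps of 10%, 60 × 1.10³ = 79.9 and 60 × 1.10⁴ = 87.8, so four steps; with steps of 5%, 60 × 1.05⁶ = 80.4, so six. Sessions 4–11 offer eight, all before the first added interval at session 16. This is a fair alternative reading. But the minimum RPM stands under the heading for raising TPO, with nothing to confine it to session 3, so the text leaves both readings open.
- **Week 6 resets intensity.** A new MPO6 is used to set loads for the second mesocycle, and the test accommodates 60–70 RPM. That makes 29 sessions at the starting load unlikely. Nothing in that section lifts the Table 1 criterion, however.
- **The share is unknown.** No arm-level under-dosing or dilution of the primary outcomes can be shown without it. Table 2 shows no cadence criterion, so phase 2 is not affected in the same way.
- **Fidelity.** A reader might also infer that the fidelity comparison is biased against HIIT. A cadence that the protocol allows can reasonably count as within prescription, and a MICT participant who loses cadence has intensity cut, which is itself a modification. Only an ambiguity remains.
- **Centres.** Providers are trained for standardisation, so a difference between centres is a risk and not an established fact.

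**Conclusion.** The contradiction holds. HIIT participants on the permitted 60–70 RPM cannot meet the printed 80 RPM criterion. Read literally, that blocks both the step to 80% of MPO6 and the added intervals, unless an instructor overrides. The Borg cycle strength test adapts its cadence limit for the same people and Table 1 does not, which suggests an oversight.

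The consequence is that affected participants may be under-dosed or progressed inconsistently. The 34% loss of phase 1 interval work is a per-participant worst case under the assumptions listed above. At arm level the mean session-3 target falls by about 0.5–7.5% for assumed shares of 2–30% with no override, so the effect is modest unless the low-cadence share is large. Permanent exclusion from progression, an under-dosed arm and a biased fidelity comparison are not shown. The point deserves correction because it concerns the dose under comparison, in one arm only, and is cheap to settle.

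**What to change.** Reconcile the lower-cadence allowance, the general and duration criteria in Table 1, and the override paragraph. Table 1 should state which cadence criterion governs power progression, and through it the added intervals, for HIIT participants on the permitted lower cadence. It should also say whether the general criteria apply at every # step or only up to session 3. The cadence value is for the investigators to decide, and none is proposed here. In the Feasibility of interventions section, state whether training at the permitted cadence counts as a fidelity deviation.

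The cost is a table footnote, one clarifying sentence on fidelity and an instructor briefing at both centres. Enrolment has begun, so trial staff should also review how any participants already trained at the lower cadence were progressed and record their number, which would replace the assumed 2–30% with a known share.

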### Active control arm: MICT

Participants in the active control arm will perform MICT designed following the current guidelines for moderate-intensity continuous exercise in both people with COPD and healthy older adults [9]. The MICT includes 20 min at a TPO of 50% of MAP with a target pedalling cadence of 60–70 RPM. Would a participant not be able to keep the target cadence, the intensity will be reduced to approximately 50% of the TPO until the cool-down phase.

Including warm-up and cool-down, the total session duration is 30 min. The intensity and duration of the 20-min exercise phase will be progressed according to general methods for MICT exercises. The initial TPO of 50% of MAP is considered a familiarization session, and the intention is to increase the intensity to 60% of MAP in session 3. As for supramaximal HIIT, the escalation of TPO in the MICT will be based on the criteria outlined in Table 1. The MICT has been chosen as an active comparator because we want to compare supramaximal HIIT to the current guidelines [9] for endurance exercise in both people with COPD and healthy older adults.

### Phase 2

#### Maintenance program

Following the first 12-week training period, participants with COPD will enter a 21-month maintenance phase (Table 2). After 2 weeks with outcome assessments and 1 to 2 weeks of rest, they will continue to exercise using the same training modality (supramaximal HIIT or MICT) as during the first 12 weeks but can select between three different settings to continue their training: ‘ Home’, ‘ Outpatient’, or ‘ Mix’ setting. The participant can, at any time during the maintenance period, change between the ‘ Home’, ‘ Outpatient,’ or ‘ Mix’ setting when conducting their endurance training. A description of each setting is provided below. Importantly, these different settings should not be seen as different trial arms. That is, irrespective of whether a participant in the supramaximal HIIT or MICT group selects to continue their training at home, in an outpatient setting or in a mixed setting, data analysis will be conducted per allocated trial arm (supramaximal HIIT, MICT, usual care).

**Table 2 Tab2:** Overview of exercise progression and progression criteria for supramaximal HIIT and MICT during phase 2

Block	Week	Session	HIIT	MICT	HIIT-Walk	MICT-Walk	General progression criteria		
	**13–14**	**Testing after 12-week intervention**					Criteria for progression are evaluated every two-week period by the research group		
**Mesocycle 1:** Focus on duration and intensity	15–18	1–8	#	**¤**	##	¤¤			
	19–22	9–16	+ 1–2 intervals	+ 2–4 min	+ 1–2 intervals	+ 2–4 min	**HIIT (outpatient, home, or mix)**		
	23–26	17–24	#	**¤**	##	¤¤	TPO (#) / duration		
	27–30	25–32	+ 1–2 intervals	+ 2–4 min	+ 1–2 intervals	+ 2–4 min	RPE ≤ 14 and dyspnoea ≤ 3 RPE 15–17 and dyspnoea 4–7 RPE 18 or dyspnoea 8 RPE 19 or dyspnoea 9 RPE 20 or dyspnoea 10	+ 5 to 10% or 2 intervals + 2.5 to 5% or 1 interval Keep same -2.5 to -5% or 1 interval -5 to -10% or 2 intervals	
	31–34	33–40	#	**¤**	##	¤¤			
	35–38	41–48	+ 1–2 intervals	+ 2–4 min	+ 1–2 intervals	+ 2–4 min	Note: Increase of HIIT intervals: max + 10 intervals for a total of 20 intervals. If reached, only intensity will increase		
	39–42	49–56	#	**¤**	##	¤¤	**MICT (outpatient, home, or mix)**		
	43–46	57–64	+ 1–2 intervals	+ 2–4 min	+ 1–2 intervals	+ 2–4 min	TPO (**¤**) / duration		
	47–50	65–72	#	**¤**	##	¤¤	RPE ≤ 11 and dyspnoea ≤ 3 RPE 12–13 and dyspnoea 4–5 RPE 14 or dyspnoea 6 RPE 15 or dyspnoea 7 RPE ≥ 16 or dyspnoea ≥ 8		+ 5 to 10% or 4-min + 2.5 to 5% or 2-min Keep same -2.5 to -5% or 2-min -5 to -10% or 4-min
	51–54	73–80	+ 1–2 intervals	+ 2–4 min	+ 1–2 intervals	+ 2–4 min			
**Mesocycle 2:** Focus on intensity	55–58	81–88	#	**¤**	##	¤¤	Note: Increase of MICT duration: max + 30 min, for a total of 50 min. If reached, only intensity will increase		
	59–62	89–96	#	**¤**	##	¤¤	**HIIT-Walk (home or mix)**		
	63–66	97–104	#	**¤**	##	¤¤	Intensity (##) / duration		
	67–70	105–112	#	**¤**	##	¤¤	RPE ≤ 14 and dyspnoea ≤ 3 RPE 15–17 and dyspnoea 4–7 RPE 18 or dyspnoea 8 RPE ≥ 19 or dyspnoea ≥ 9	↑speed or + 2 intervals + 1 interval Keep same ↓ speed or -1 interval	
	71–74	113–120	#	**¤**	##	¤¤			
	75–78	121–128	#	**¤**	##	¤¤	Note: Increase of HIIT-Walk intervals: max + 10 intervals, for a total of 20 intervals. If reached, only intensity will increase		
	79–82	129–136	#	**¤**	##	¤¤	¤¤ **MICT-Walk** **(home or mix)**		
	83–86	137–144	#	**¤**	##	¤¤	Intensity (¤¤) / duration		
	87–90	145–152	#	**¤**	##	¤¤	RPE ≥ 11 and dyspnoea ≤ 3 RPE 12–13 and dyspnoea 4–5 RPE 14 or dyspnoea 6 RPE ≥ 15 or dyspnoea ≥ 7	↑speed or + 4 min + 2 min Keep same ↓ speed or -2 min	
	91–94	153–160	#	**¤**	##	¤¤			
	95–98	161–168	#	**¤**	##	¤¤	Note: Increase of MICT-Walk duration: max + 30 min, for a total of 50 min. If reached, only intensity will increase		
	99–102	169–176	#	**¤**	##	¤¤			
	**103–104**	**Testing after 21-month maintenance**							

An overview of the intensity, duration, and their progression criteria to be used in phase 1. The actual number of weeks displayed in the table do not include the one to two rest weeks after phase 1. # and ## indicates progression of intensity in supramaximal HIIT and HIIT-Walk, respectively, based on criteria outlined in the table. ¤ and  ¤ ¤ indicates progression of intensity in MICT and MICT-Walk, respectively, based on criteria outlined in the table. *HIIT* supramaximal high-intensity interval training, *MICT* moderate-intensity continuous training, *TPO* target power output

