#### Home

Participants with COPD that select to continue with endurance training in a home setting will be provided with a cycle ergometer (Smart ZBike, Zycle, Valencia, Spain) for unsupervised supramaximal HIIT or MICT. Alternatively, if a participant would like to continue at home but does not want to receive a cycle ergometer, they can continue with walking-based HIIT or MICT (HIIT-Walk or MICT-Walk). The HIIT-Walk and MICT-Walk build on the same principles as the supramaximal HIIT and MICT exercise performed on a cycle ergometer but are modified to be suitable during walking. See Tables 2 and 3 for details.

**Table 3 Tab3:** Description of Endurance Training (ET) in line with TIDieR and CERT guidelines

Variable	Supramaximal HIIT	MICT	HIIT-Walk	MICT-Walk
1. ET objective	The ET objective for all interventions is to improve peak VO_2_ on a CPET and exercise duration on a CWRT.			
2. Training device / type of exercise	Cycling on a stationary cycle ergometer (Smart Zbike, Zycle, Valencia, Spain)		Outdoor walking	
3. Supervision and delivery	First 12 weeks and outpatient last 21 months: Group of 4-5 individuals under the supervision of a trained instructor^a^, face-to-face delivery / Home or mix last 21 months: unsupervised cycling, individual, phone call delivery every two weeks		Unsupervised walking training, individual, phone call delivery every two weeks	
4. Setting	First 12 weeks: outpatient (local gym or rehab center) / Last 21 months: Home, outpatient (local gym or rehab center) or mix (local gym or rehab center + home)		Home	
5. Adjunct	First 12 weeks: none / Last 21 months: RT (see Table 4)		RT (see Table 4)	
6. Program duration	12 weeks + ≈ 21 months		≈ 21 months	
7. Frequency of sessions	Week 1-6: 2x/week / Week 7-12: 3x/week / Week 15 to 102: 2x/week		Week 15 to 102: 2x/week	
8. Exercise selection	10×6 sec intervals against an individualized intensity with 48 sec recovery^b^ between intervals (20s passive, 28s active) for 10 min	Continuous cycling against an individualized intensity for 20 min	10×10 sec intervals at an individualized maximal walking speed with 50 sec of active rest between intervals for 10 min	Continuous walking at an individualized intensity for 20 min
9. Warm-up / cool-down	5 min at 30% of MAP at 50-70 RPM^c^		5 min at a walking speed at Borg dyspnea <3	

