10. Intensity	Start intensity of 60% of MPO_6_ with aim of increasing up to 80% of MPO_6_ in session 3.	Start intensity at 50% of MAP with aim of increasing up to 60% of MAP in session 3.	Start intensity at a walking speed as tolerated at Borg dyspnea 4-8 at the end of the last interval	Start intensity at a walking speed as tolerated at Borg dyspnea 4-6 at the end of the last minute
11. Exercise volume	Exercise volume will be evaluated by: duration (min:ss), training load in kilojoule (intensity × duration), duration at intensity above MAP (mm:ss)		Cannot be accurately calculated	
12. Velocity of muscle action	80-90 RPM	60-70 RPM	Self-determined walking speed at Borg dyspnea 4-8 and 4-6 for HIIT-Walk and MICT-Walk, resp.	
13. Rest periods between series / type of rest incl. intensity	20 sec passive, 28 sec active rest at 30% of MAP between intervals	N/A	50 sec of active rest at Borg dyspnea < 3	N/A
14. Rest / sequence between exercises	If ET and RT are performed on the same day, a minimum of 15 min rest between ET and RT, and ET is performed first			
15. Recovery	At least 48h rest between sessions			
16. Attendance (% of sessions) / Adherence^d^	Completion rate, attendance rate, and adherence to exercise duration and intensity will be obtained.			
17. Specificity	Variables 6-16 are designed to achieve the ET objective (Variable 1)			
18. Progressive overload	Progression/overload criteria are seen in Table 1- 2		Progression/overload criteria are seen in Table 2	
19. Variation	Non-linear block periodization			
20. Individuality	Designed to lower the ventilatory demand, based on BCST data to set intensity	Designed per ATS/ERS guidelines^9^, based on CPET data to set intensity	N/A	N/A

*CPET *cardiopulmonary exercise test,* CWRT *constant-workload test,* ET* endurance training, *ATS/ERS* American Thoracic Society/European Respiratory Society, *MICT* moderate intensity continuous training, *HIIT* high-intensity interval training, *MPO*_*6*_ maximal mean power output for six seconds, *N/A* Not applicable, *RPE* rating of perceived exertion, *RPM* revolutions per minute, *RT* resistance training

^a^The instructor education consists of written, oral and visual instructions on how to perform HIIT & MICT exercises, and instructors are qualified health professionals (e.g. physiotherapists, exercise physiologists)

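### Table 2 prints the top MICT-Walk progression row with the wrong sign (RPE ≥ 11 instead of ≤ 11), so some hard sessions call for both an increase and a decrease, and the easiest sessions match no row

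*Protocol article*

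**What the plan says.** Table 2 (Maintenance program) sets out how endurance training progresses in phase 2. MICT-Walk has four rows, with the actions, in order: raise speed or add 4 min; add 2 min; keep the same; lower speed or take off 2 min. The first two rows are "RPE ≥ 11 and dyspnoea ≤ 3 RPE 12–13 and dyspnoea 4–5" and the last two are "RPE 14 or dyspnoea 6 RPE ≥ 15 or dyspnoea ≥ 7".

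In the same table, the first two rows for cycling MICT are "RPE ≤ 11 and dyspnoea ≤ 3 RPE 12–13 and dyspnoea 4–5". The Home section says that the walking versions "build on the same principles as the supramaximal HIIT and MICT exercise performed on a cycle ergometer". Table 3, item 18, refers the walking modes to Table 2 alone for their progression criteria. Table 1 carries a note that "The highest rating informs the progression decision"; Table 2 does not repeat it.

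**The concern.** A row that grants the largest increase should apply when the session felt easy. As printed it applies from RPE 11 upwards, with no upper limit, as long as dyspnoea is 3 or less. A session rated very hard for exertion but with little breathlessness then qualifies for the largest increase and for a decrease together, while a session rated easy on both scales matches nothing.

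These rows control dose in a setting with little other control. Table 3 describes walking as unsupervised, followed up by phone every two weeks, and accepts that its exercise volume cannot be worked out accurately. Read literally, the rule could push some participants the wrong way and leave those who find the walk easiest without any progression.

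**Working it through.** There is no sample size or power figure behind this point, so the check has two parts.

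**1. Is the sign a misprint?** The parallel top rows are:

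| Mode | Table | RPE condition | Dyspnoea condition |
|---|---|---|---|
| Cycling MICT, phase 1 | 1 | ≤ 11 | ≤ 3 |
| Cycling MICT, phase 2 | 2 | ≤ 11 | ≤ 3 |
| Supramaximal HIIT | 1 and 2 | ≤ 14 | ≤ 3 |
| HIIT-Walk | 2 | ≤ 14 | ≤ 3 |
| MICT-Walk | 2 | **≥ 11** | ≤ 3 |

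MICT-Walk is the only exception. Its other rows climb through RPE 12–13, 14 and ≥ 15, so the row above them has to cover the values below 12. The other signs in the same cell are sensible, so a fault in reading the PDF is unlikely.

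**2. What does the sign do?** The Outcomes section gives the scales as RPE 6–20 (15 whole values) and dyspnoea 0–10 (11 whole values), which makes 15 × 11 = 165 pairs. Each pair was tested against the four MICT-Walk rows, with no tie-break.

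| Pairs that meet | As printed (≥ 11) | Corrected (≤ 11) |
|---|---|---|
| Raise and lower | RPE 15–20, dyspnoea 0–3: 6 × 4 = 24 | 0 |
| Raise and keep | RPE 14, dyspnoea 0–3: 1 × 4 = 4 | 0 |
| Keep and lower | 4 + 6 = 10 | 10 |
| No row, easiest ratings (RPE 6–10, dyspnoea 0–3) | 5 × 4 = 20 | 0 |
| No row, RPE 6–11 with dyspnoea 4–5 | 6 × 2 = 12 | 12 |
| No row, RPE 12–13 with dyspnoea 0–3 | 0 | 2 × 4 = 8 |
| No row, total | 32 | 20 |

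The 10 keep-and-lower pairs are RPE 14 with dyspnoea 7–10 (4) and dyspnoea 6 with RPE 15–20 (6). The sign does not affect them.

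**Would the Table 1 note be enough on its own?** If the higher rating decides, the 24 + 4 = 28 conflicting pairs follow RPE and resolve to lower or keep. The 20 easiest pairs stay without a rule, because as printed no row covers RPE 6–10 at dyspnoea 0–3. The sign itself must change.

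**Does the corrected sign need the note?** Yes. The 20 mixed pairs left over (12 + 8) are the same 20 that the correctly printed cycling MICT rows in Table 2 leave open. Under the note, each follows its higher rating to the second row (add 2 min).

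**A separate small overlap in Table 1.** Among the cycling MICT workload rows, "RPE ≥ 15 or dyspnoea 7" (reduce by 2.5 to 5%) also covers RPE 16–20, which the next row (RPE ≥ 16 or dyspnoea ≥ 8) reduces by 5 to 10%. Both rows cut the load, so only the size of the cut is unclear. Table 2 prints RPE 15 in the corresponding place.

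**The case against.** The strongest reply is that the misprint corrects itself. Every neighbouring row shows what was meant, and a trained instructor would not raise the dose of someone rating 18. Participants do not apply the table themselves: "Criteria for progression are evaluated every two-week period by the research group", using information from standardised calls whose script is in an additional file not shown here. The wrong sign may never have reached a working instruction. All 48 affected pairs (24 + 4 + 20) also have dyspnoea 0–3, below the prescribed "Self-determined walking speed at Borg dyspnea 4-8 and 4-6 for HIIT-Walk and MICT-Walk, resp". Within dyspnoea 4–6 the printed and corrected tables agree. The count weights all pairs equally, although nobody knows how often each occurs, and the corrected sign still leaves 20 pairs without a row.

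Most of this stands as a limit on the size of the problem. The article does not show that anyone was given the wrong dose, and the pair counts describe the rule's logic, not its use. It does not make the printed row right. The row is written for dyspnoea 3 or less, so ratings below the prescribed range are exactly the ones it must handle. Gaps in cycling MICT do not excuse a reversed sign in walking. The Table 1 overlap is minor, since the note there sensibly points RPE 16 or more to the larger cut.

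**Conclusion.** The concern holds. The top MICT-Walk row in Table 2 is wrong as printed and should read RPE ≤ 11. Of 165 possible rating pairs, 28 receive conflicting instructions (24 raise and lower, 4 raise and keep), and the 20 easiest receive none. The correction removes all 28 conflicts and gives all 20 easiest pairs the largest increase.

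The practical weight is low. Only MICT participants who choose walking in phase 2 are exposed, with review every two weeks. Phase 1, the sample size and the analysis are unaffected. The conclusion assumes whole-number ratings and a literal reading of the rows; the document does not say how often the affected ratings occur. It is worth fixing because the row is an operative dose rule and the repair costs almost nothing.

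**What to change.** - In Table 2, change the top MICT-Walk row to RPE ≤ 11 and dyspnoea ≤ 3.
- Repeat the highest-rating note under Table 2, so that mixed ratings are settled for walking and cycling alike.
- Check that the progression sheets and call scripts in use at both centres carry the corrected sign.
- As a minor tidy-up, print RPE 15 or dyspnoea 7 in the Table 1 MICT workload rows, as Table 2 does, so that RPE 16 or more maps only to the 5 to 10% reduction.

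The cost is one sign and one repeated note in Table 2, one sign in Table 1, and a check of documents at two centres. Design, sample size and analysis do not change.
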